### Trial objective

The primary objective of the present trial is to determine the efficacy and safety of oral ingestion of an existing oral Chinese herbal formula (Pei Tu Qing Xin granules; PTQX) on symptom severity and improvement in health-related quality of life (QoL) in children aged between 6 and 16 years with moderate to severe AE. We will also assess the safety of PTQX for AE.

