### Sample size

Calculation of the sample size of this trial was based on the effect size of the primary outcome, Eczema Area and Severity Index (EASI) score, reported in a previous published study [18]. The means and standard deviations (SDs) of the EASI scores were 7.4 ± 3.3 and 9.6 ± 4.1 for the active treatment and control groups, respectively. To achieve 90 % power (β = 0.10), significance level of 0.05 (α) in a two-tailed test, calculated by using G*Power 3.1.2 (http://www.gpower.hhu.de/en.html), 62 participants, based on an estimated 10 % dropout rate, are needed for each group. That makes a total of 124 for the main trial. A pilot study with 30 participants (15 per group) conducted in RMIT University will provide preliminary data on the clinical efficacy of PTQX based on EASI score and will allow us to monitor for adverse events. The mean and SD of EASI score from the pilot study will be used for recalculation of the sample size for the main trial.

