### Outcome measures

Current recommendations for outcome measurement in RCTs of AE include clinical signs and symptoms, long-term control of flares and health-related QoL [19]. This trial will adopt these recommendations for its outcome measures. The primary outcome measure is change in clinical signs severity based on EASI score. Secondary outcome measures include change in symptoms using the Patient-Oriented Eczema Measure (POEM) [20], health-related QoL using the Children’s Dermatology Life Quality Index (CDLQI) [21], use of concomitant medicines (number of days used and total dosage for corticosteroids) and adverse events and safety (pathology tests).

The EASI, POEM, CDLQI, concomitant medications and adverse events will be recorded at visit 1 (week 0), visit 2 (week 4), visit 3 (week 8), visit 4 (week 12) and visit 5 (week 16). Pathology tests (full blood examination with eosinophil count and immunoglobulin E, liver and renal function tests) will be performed by a qualified phlebotomist at the screening (week −2) and at the second (week 4) and fourth (week 12) visits. Medical advice from a medical officer will be sought for any serious adverse events or for any serious aggravation of the existing skin condition or abnormal pathology results during the trial period.

Any adverse events will be managed in compliance with the guidelines of the *Note for Guidance on Clinical Safety Data Management: Definitions and Standards for Expedited Reporting (CPMP/ICH/377/95)* issued by TGA [22]. A serious adverse event will be reported to the RMIT HREC within 24 hours and then to the TGA within 7–15 days. Table 1 summarises the schedule of the trial and outlines the time points of outcome measures of the trial.

**Table 1 Tab1:** Schedule of the trial

Items	Screening/run-in period	Visit 1 (baseline)	Visit 2	Visit 3	Visit 4 (endpoint)	Visit 5 (follow-up)
Week of the trial	−2/−1	0	4	8	12	16
Demographic information-taking	+					
Informed consent form (PICF)	+					
General medical history-taking	+					
Severity of AE for inclusion and exclusion of the participants (NESS)	+					
Blood tests	+		+		+	
Clinical sign of AE (EASI)		+	+	+	+	+
Symptoms (POEM)		+	+	+	+	+
QoL score (CDLQI)		+	+	+	+	+
Distributions of treatment or placebo products		+	+	+		
Daily medical record	+	+	+	+	+	+
Monitor of adverse event		+	+	+	+	+
Compliance check		+	+	+	+	+
Survey of participation						+

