### Statistical analysis

Data will be analysed by an independent statistician using IBM SPSS version 22 software (IBM, Armonk, NY, USA). Comparison of means of continuous variables (i.e., EASI, POEM and CDLQI scores) will be expressed as differences in means with 95 % confidence intervals (CIs). One-way analysis of variance will be used for normally distributed data, and nonparametric tests will be used for skewed distribution data. χ^2^ or Fisher’s exact tests will be performed for comparison of dichotomised data, and dichotomous data will be expressed as risk ratios with 95 % CIs. All comparisons will be two-tailed, with *p* values <0.05 considered to be statistically significant.

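### Safety is in the primary objective, but a risk ratio with a p<0.05 test gives no estimate when placebo has no events and has little power for rare or modest harms; add risk differences with intervals

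*Protocol article*

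**What the plan says.** - **Objective.** Under Trial objective, safety stands beside efficacy: "The primary objective of the present trial is to determine the efficacy and safety of oral ingestion".
- **Outcome.** Under Outcome measures, "adverse events and safety (pathology tests" closes the list of secondary outcomes. The same section provides for medical advice on serious events and abnormal results, and for reporting to the ethics committee and the regulator.
- **Size.** Under Sample size, the calculation uses EASI only: "EASI scores were 7.4 ± 3.3 and 9.6 ± 4.1 for the active treatment and control groups". It arrives at 62 per group. A pilot of 15 per group "will allow us to monitor for adverse events".
- **Analysis.** Under Statistical analysis, chi-squared or "Fisher’s exact tests will be performed for comparison of dichotomised data", and "dichotomous data will be expressed as risk ratios with 95 % CIs". One threshold covers everything: "All comparisons will be two-tailed, with *p* values <0.05 considered to be statistically significant".

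EASI, POEM and CDLQI are named there as continuous variables, and concomitant medicine use is measured in days and dosage. The rule for binary data therefore falls almost wholly on adverse events and abnormal pathology results, although the section does not name them.

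**The concern.** A safety objective asks how much excess harm the data can rule out. The stated method looks for a difference and expresses it as a ratio. Two things follow when events are few.

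First, a ratio with zero in the denominator does not exist, and the usual interval on the log scale does not exist either. Serious events and marked liver or renal abnormalities may well be sparse, because children with liver or renal dysfunction are excluded. In that situation the p value is all that remains of the stated analysis.

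Second, the sample size was never set with harm in mind, so a non-significant p value is a likely result even if a rare or modest excess is real. The trial could then report no significant difference in adverse events for an oral product in children while a material excess risk remained compatible with its data.

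**Working it through.** **The plan's own figure.** Pooled SD = √[(3.3² + 4.1²)/2] = 3.72; d = (9.6 − 7.4)/3.72 = 0.591. A two-sided t-test at 0.05 with 90 % power needs 62 per group (normal approximation: 2(1.960 + 1.282)²/0.591² = 60.1, rounded up to 61). The stated 62 is thus the number before dropout; with 10 % dropout it would be 62/0.9 = 69. That is a separate matter. Here it shows that EASI alone set the size. I use 62 per arm, 56 per arm after 10 % loss, and 15 per arm for the pilot.

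**Assumption.** The article gives no adverse event rates. Every rate below is assumed, and a range is shown.

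**Chance that the risk ratio cannot be computed.** P(no placebo events) = (1 − p)ⁿ.

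| Placebo rate | n = 62 | n = 15 |
|---|---|---|
| 1 % | 0.99⁶² = 54 % | 86 % |
| 2 % | 0.98⁶² = 29 % | 74 % |
| 5 % | 0.95⁶² = 4 % | 46 % |
| 10 % | 0.90⁶² = 0.1 % | 21 % |

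**Chance that a real excess gives p ≥ 0.05.** All binomial outcomes were enumerated exactly with the two-sided test at 0.05. The mixed column uses chi-squared when every expected count is at least 5 and Fisher otherwise. That is a common convention and my assumption, because the article does not say when each test applies.

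| Placebo v PTQX | Fisher, 62 | Mixed, 62 | Fisher, 56 | Fisher, 15 |
|---|---|---|---|---|
| 5 % v 10 % | 91 % | 85 % | 92 % | 99 % |
| 5 % v 15 % | 66 % | 55 % | 71 % | 97 % |
| 10 % v 20 % | 74 % | 66 % | 78 % | 96 % |
| 5 % v 20 % | 35 % | 26 % | 42 % | 92 % |
| 20 % v 40 % | 38 % | 31 % | 43 % | 89 % |
| 10 % v 30 % | 25 % | 19 % | 31 % | 85 % |

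**Example with an empty placebo cell: 5/62 v 0/62.**
- Risk ratio: division by zero.
- Fisher p = 0.057; uncorrected chi-squared p = 0.022.
- Risk difference = 5/62 = 8.1 points. Wilson 95 % limits are 3.5 % to 17.5 % for PTQX and 0 to 5.8 % for placebo.
- Newcombe lower limit: 0.081 − √[(0.081 − 0.035)² + 0.058²] = 0.007. Upper limit: 0.081 + (0.175 − 0.081) = 0.175. The interval is 0.7 to 17.5 points.

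**Example with events in both arms: 3/62 v 1/62.** RR = 3.0; SE of log RR = √(1/3 − 1/62 + 1 − 1/62) = 1.141; 95 % CI = 3.0 × exp(±1.96 × 1.141) = 0.32 to 28.1. An upper limit exists, but it is wide.

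**What zero events can exclude.** The exact one-sided 95 % upper limit is 1 − 0.05^(1/n): 4.7 % for 0/62, 5.2 % for 0/56 and 18.1 % for 0/15.

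**The case against.** The strongest reply is that the article states no safety criterion at all. Its analysis section is a general rule for binary data, its threshold defines statistical significance and not safety, and a risk ratio with an interval is conventional. Sizing on the efficacy outcome is also standard, and low power for rare harm is shared by any trial of 124. Empty-cell handling and adverse event tables are usually settled in a full protocol or analysis plan, neither of which is shown.

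Much of this stands, and it rules out three stronger readings that a reader might infer:

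- **That p<0.05 is the rule by which safety is decided.** The article never says so. Serious events and abnormal results are reviewed individually and reported without waiting for a p value.
- **That harm is left without any upper bound.** This is true of the ratio only when placebo has no events. With at least one event in each arm, the promised interval has an upper limit.
- **That a real harm will usually be missed.** This depends on rates the article does not give. It fails for large, common excesses: 10 % v 30 % is missed 19 % to 25 % of the time at 62 per arm.

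The reply does not remove the point. The article positively chooses the risk ratio for binary data, and that choice fails when the placebo arm is empty. Individual case review protects the children in the trial, but it does not compare the arms or answer the stated objective.

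**Conclusion.** The point holds as a limited one. Safety is named in the primary objective, appears as a secondary outcome, and is served by a summary that breaks down with sparse events and a test with little power for rare or modest excess harm at 62 per arm. The size depends on assumed rates. The ratio is unavailable with probability 54 % at a 1 % placebo rate but only 4 % at 5 %. Fisher misses 5 % v 10 % about 91 % of the time and chi-squared somewhat less often, while large, common excesses are usually found. The pilot, at 15 per arm, can say very little about harm by significance testing. A non-significant result in either study should not be read as evidence of safety. The article does not say that it would be; it leaves that reading open. This is a cheap improvement to the analysis and does not invalidate the design.

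**What to change.** In Statistical analysis, add that for adverse events, serious adverse events and abnormal pathology results:

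1. Counts and risks will be reported per arm.
2. The risk difference (PTQX minus placebo) will be given with a Newcombe or score 95 % interval, alongside the risk ratio where it can be estimated.
3. When an arm has no events, the exact one-sided 95 % upper limit of its event rate will be given.
4. The safety conclusion rests on these intervals, and p>0.05 will not be taken as evidence of safety.

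The same edit can settle whether safety is a primary or a secondary matter, so that Trial objective and Outcome measures agree.

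The cost is a few sentences and a short extra calculation, with no more participants or procedures. The safety statement becomes more cautious. The interval and the Fisher p value will sometimes disagree, as they do for 5/62 v 0/62, so the text should say beforehand that the interval is the basis for interpretation.

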## Discussion

Determination of the trial timeline is one of the challenges of the trial design. It depends on many factors, such as how long the effect of the intervention may last, costs of the trial and tolerability by and compliance of the participants. The trial duration of 16 weeks has been determined after consideration of these issues. This protocol was developed according to the guidelines of *Australian Clinical Trial Handbook* [23] and follows the *nine CONSORT checklist items for RCTs of herbal medicines* [24]. Key elements for conducting a high-quality RCT, such as randomisation, sequence generation, allocation concealment, blinding methods, proper sample size, compliance with protocol, determination of baseline and endpoint and adequate outcome measures have been addressed.

## Trial status

Participant recruitment commenced on 31 March 2015. It is anticipated that the trial will be completed in February 2016.

## Abbreviations

AE: Atopic eczema
ANZCTR: Australian New Zealand Clinical Trials Registry
CDLQI: Children’s Dermatology Life Quality Index
CHM: Chinese herbal medicine
CI: Confidence interval
CONSORT: Consolidated Standards of Reporting Trials
CTN: Clinical Trial Notification
EASI: Eczema Area and Severity Index
GP: General practitioner
HREC: Human Research Ethics Committee
IL: Interleukin
NESS: Nottingham Eczema Severity Score
PICF: Participant information and consent form
POEM: Patient-Oriented Eczema Measure
PTQX: Pei Tu Qing Xin granules
QoL: Quality of life
RCT: Randomised clinical trial
RMIT: Royal Melbourne Institute of Technology
SD: Standard deviation
TGA: Therapeutic Goods Administration
